#### Recruitment

Young people will be recruited from Child and Adolescent Mental Health Services (CAMHS; Tiers 2 and 3), other Tier 2 services, and GP practices (Tier 1). Tier 2 services may be provided by NHS Trusts, but in some areas they are provided by the third sector (e.g. in Norfolk and Suffolk, Point 1 provide these services). The main organisation at each site is likely to be CAMHS (with responsibility to ensure clinical safety), with independent Tier 2 and GP practices acting as participant identification centres (PIC). The English counties involved are Hertfordshire (Hertfordshire Partnership University NHS Foundation Trust and Hertfordshire Community Trust), Norfolk (Norfolk & Suffolk NHS Foundation Trust), and Bedford (East London NHS Foundation Trust). These sites will be involved in recruitment to the study including screening and gaining consent from participants and collection of study outcome measures at baseline and follow-up. Effort was made to base the study across counties that would broaden the characteristics of the sample in terms of race/ethnicity and indices of deprivation.

### Assignment of interventions

Eligible participants who have consented to the study will be allocated to groups of approximately 9 participants, and each group will be randomised into one of the three trial arms (Table 3). This clustering is designed to limit waiting time for young people to start the intervention to minimise the dropout rate. Each group will either be a single-sex group or will include at least two girls and two boys. The former was deemed essential by patient and public involvement (PPI) representatives from diverse cultural heritage.

**Table 3 Tab3:** Study schedule

	Study period						
	Screening	Randomisation	Post-randomisation				Post-randomisation follow-up
TIMEPOINT	Pre-T0	Pre-T0	T0	T0-T1	T1 +14 weeks	T2 +26 weeks	
**ENROLMENT:**							
**Eligibility screen**	X						
**Referral to research team**	X						
**Informed consent**	X						
**Randomisation**		X					
**INTERVENTIONS**				X			
**ASSESSMENTS:**							
***CDI-2***	X		X		X	X	
***Demographic information***	X						
***DAWBA (includes SDQ) CYP completed***	X						
***DAWBA (includes SDQ) Carer completed***	X						
***PAR-Q***	X						
***PANAS***			X		X	X	
***Self-efficacy scale***			X		X	X	
***Social Support Scale***			X		X	X	
***Caregiver burden***			X		X	X	
***Adherence***				X			
***Peak and average HR***				X			
***Ratings of Perceived Exertion***				X			
***Measured physical activity***			X		X	X	
***Y-PAQ***			X		X	X	
***COM-B measures***			X		X	X	
***EQ-5D-5L***			X		X	X	
***CSRI***			X		X	X	
***CHU-9D***			X		X	X	
***Focus groups***							X
**ADVERSE EVENT MONITORING**			X	X	X	X	X

Note: *FU* follow-up, *T0* baseline, *T1* first FU, *T2* second FU, *CDI-2* Clinical Depression Inventory – 2, *DAWBA* Development and Wellbeing Assessment, *SDQ* Strengths and Difficulties Questionnaire, *CYP* Child or Young Person, *PAR-Q* Physical Activity Readiness Questionnaire, *PANAS* Positive and Negative Affect Schedule, *Y-PAQ* Youth Physical Activity Questionnaire, *CSRI* Client Service Receipt Inventory, *CHU-9D* Child Health Utility 9D

#### Sequence generation

The allocated treatment for a group will be generated via computer written code using stratification with random permuted blocks. Stratification will be by study site.

#### Allocation concealment mechanism

The groups will be allocated to the intervention by a process embedded in the web-based data management system. When a group is randomised, an email will be sent to the principal investigator (PI), the Trial Manager, the MHSW, and the REP for them to set up the appropriate intervention.

#### Implementation

All participants who give consent for participation and who fulfil the inclusion criteria will be randomised. Randomisation will be performed centrally by the study manager using an online bespoke randomisation module provided and managed by Norwich Clinical Trials Unit (NCTU). The allocation sequence will be generated by the NCTU applying a permuted block design with random blocks stratified by study centre. The randomisation list remains with NCTU for the whole duration of the study. Thus, randomisation will be conducted without any influence of the principal investigators, MHSWs, or REPs.

#### Blinding (masking)

Due to the nature of the intervention, neither participants nor delivery staff can be blinded to allocation. However, it may be possible for the baseline and outcome assessments to be collected using a single blind (researcher) approach. Outcome assessment questionnaires will be completed online using mobile phones or tablets. However, it is anticipated that some young people may require assistance in completing the questionnaires, and therefore, we propose to evaluate the extent to which deliverers are needed to facilitate questionnaire completion at the 14- and 26-week follow-up sessions. Data will be analysed without access to information about allocation.

### Data collection, management, and analysis

#### Data collection methods

Screening data will be collected from patient notes and entered directly into the study database by members of the trial team working within each research site. Exceptionally, data may be entered onto paper case record forms prior to entry onto the database. Data collection, data entry, and queries raised by a member of the trial team will be managed in line with the NCTU and trial specific data management processes. Identification logs, screening logs, and enrolment logs will be kept at the trial site in a locked cabinet within a secured room. Patient reported screening data will be entered directly into the study database by the participant and their parent via an online questionnaire.

##### Baseline and follow-up

Young people and parents will be followed-up at 14 and 26 weeks. To maximise engagement with the young people in the study, baseline and follow-up data collection is planned as a group session (in trial groups), with the young people completing the outcome measures as online questionnaires either on their smartphones, or on tablets provided by the group facilitator. Individual follow-up via online questionnaire will be available where preferred by the young person. Caregiver burden data will be collected from parents via online survey, either at the group session or at home.

Attendance, adherence, and physical exertion data will be recorded on a paper form at each intervention session by the REP, and then entered into the study database immediately after the session has concluded. Heart rate data during the session will be recorded using chest band monitors and relayed to the REP’s tablet via Bluetooth. It will then be entered manually into the study database by the REP.

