##### Outcome measures

*Psychological measures*
Children’s Depression Inventory (CDI 2 [44];), which measures self-reported depressive symptoms in youth aged 7–17 years and takes 5–15 min to complete (primary outcome for the potential full trial)Positive and Negative Affect Schedule (PANAS [65];), with two 10-item sub-scales for positive and negative affectNew General Self-Efficacy scale [66], an eight-item measure to assess how much people believe they can achieve their goals to engage in exerciseMultidimensional scale of perceived Social Support (MSPSS [67];), a twelve-item measure designed to measure perceptions of support from family, friends, and a significant otherA six-item COM-B measure asking participants how much they agree that they have the Capability (Physical and Psychological), Opportunity (Social and Physical), and Motivation (Reflective and Automatic) to be regularly active [68].

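### Table 3 schedules baseline (T0) after randomisation, so ten of the 11 measures taken at T0 have no pre-randomisation value

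*Protocol article*

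**What the plan says.** All references are to the protocol article.

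- **Table 3, header.** Screening and Randomisation are the first two columns. The next four (T0, T0-T1, T1, T2) sit under Post-randomisation. The time-point row reads "Pre-T0 Pre-T0 T0 T0-T1 T1 +14 weeks T2 +26 weeks". The table note defines "T0* baseline, *T1* first FU, *T2* second FU".
- **Table 3, body.** Randomisation is marked in the second column, the baseline measures in the third and the intervention in the fourth.
- **Assignment of interventions.** Participants are "allocated to groups of approximately 9 participants, and each group will be randomised into one of the three trial arms", so a group exists before its arm is drawn.
- **Allocation concealment mechanism.** "When a group is randomised, an email will be sent to the principal investigator (PI), the Trial Manager, the MHSW, and the REP", so that they can set up the arm.
- **Implementation.** Everyone who consents and meets the inclusion criteria is randomised. Completing baseline is not made a condition.
- **Baseline and follow-up.** "baseline and follow-up data collection is planned as a group session (in trial groups"), on the participants' own phones or on tablets from the group facilitator.
- **Blinding.** "neither participants nor delivery staff can be blinded to allocation", although "it may be possible for the baseline and outcome assessments to be collected using a single blind (researcher) approach".
- **Outcome measures and Economic evaluation.** The CDI-2 is named as "primary outcome for the potential full trial". The CSRI is filled in together with the MHSW.

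**The concern.** A baseline should be fixed before anyone involved in giving or recording it can know the arm. Here the arms differ sharply in appeal and demand (maximal-effort exercise, walking sports, or board games and discussion), and most T0 measures are self-reports. Two of them ask directly about exercise: self-efficacy for exercise goals, and the COM-B items on capability and motivation to be active. Answers to these could move once a young person knows what is coming. Activity recorded by accelerometer or Y-PAQ could move for the same reason.

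Two things are at stake. First, a baseline that has already responded to allocation makes a poor reference for describing arms or change. If learning the arm shifted one arm's mean baseline by δ relative to another, and left follow-up scores alone, a between-arm contrast in change scores would be off by δ, and a baseline-adjusted contrast by δ times the baseline slope. Second, someone who leaves on learning the arm leaves before giving any baseline on most measures.

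**Working it through.** The plan gives no figure to reproduce. The check is the order of events and a count of Table 3 rows.

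**1. Order of events.** The Table 3 header gives Screening (Pre-T0), Randomisation (Pre-T0), T0, T0-T1, T1 (14 weeks), T2 (26 weeks). The row marks agree with it, as listed above. The scheduled order is therefore randomisation, then baseline, then intervention. No text section puts baseline before allocation. The study flowchart (Fig. 1) is not shown and could not be checked.

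The statement that baseline is collected in trial groups does not establish this order by itself, because groups are formed before they are randomised. The evidence is Table 3.

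**2. Count of measures marked at T0.**

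| Measure | Screening | T0 |
|---|---|---|
| CDI-2 | X | X |
| PANAS | – | X |
| Self-efficacy scale | – | X |
| Social support scale | – | X |
| Caregiver burden | – | X |
| Measured physical activity (accelerometer) | – | X |
| Y-PAQ | – | X |
| COM-B measures | – | X |
| EQ-5D-5L | – | X |
| CSRI | – | X |
| CHU-9D | – | X |

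Marked at T0: 11. Marked at both screening and T0: 1 (CDI-2). No pre-randomisation value: 11 − 1 = 10.

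**3. The CDI-2 exception.** Its screening score precedes randomisation, but Eligibility criteria selects participants on that score (17 to 36). It is a truncated, selected value and not a clean replacement for a baseline.

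**4. Who can know the arm at T0.**
- MHSW and REP: documented. They are emailed when the group is randomised.
- CSRI: by the schedule it is completed at T0 with an MHSW who has already been told the arm. That sits badly with the hope of single-blind collection at baseline.
- Participants and carers: not documented. They cannot be blinded, no disclosure time is stated, and nothing holds the arm back until T0 is complete.

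**5. What in this trial uses these values.**
- Feasibility outcomes lists accelerometer activity at baseline, 14 and 26 weeks, and Statistical methods describes increased physical activity.
- Statistical methods summarises outcome measures by arm.
- Economic evaluation uses EQ-5D-5L and CHU-9D from baseline onward for QALYs and for choosing the main-trial instrument.
- Missing data are reported at 26 weeks net of withdrawals. A participant lost between randomisation and T0 counts towards attrition, but the missing-data proportion need not show the lost baselines.

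**The case against.** The strongest reply is that little in this trial depends on the point. The study is a feasibility trial without power for clinical outcomes. Its analysis is largely descriptive, with no formal comparison between groups. Referral, recruitment, attendance, adherence and adverse events do not depend on whether questionnaires come before or after allocation. The intended main-trial primary outcome has a screening value, and demographics and the DAWBA/SDQ are also taken at screening, so early leavers can still be described. All of this stands, and it is why the point is not rated higher.

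Three stronger readings are tempting, and the documents do not support them.

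- **That the baselines are not pre-treatment values.** Table 3 marks the intervention only in T0-T1, after T0. The values are pre-intervention; what they are not is pre-randomisation.
- **That participants complete T0 already knowing their arm.** This is a fair inference from the lack of blinding, but the time of disclosure is never stated. Only the staff notification is documented.
- **That the bias can be given a size.** The documents give neither a shift nor a baseline slope, and a shift distorts a contrast only if it differs between arms. The measures will also differ in susceptibility. The CSRI asks about service use over the previous 12 weeks, which hearing the arm should hardly change.

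The possible single-blind approach does not answer the point. It is only a possibility, and a blinded researcher does not blind a young person or carer who reports on themselves.

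**Conclusion.** The point holds as one about scheduling, with moderate severity. By Table 3, all 11 T0 measures are taken after randomisation, and ten have no earlier value for any of the planned 81 participants. The remaining one has an earlier value that doubles as the eligibility score. The order of events and the count are firm, subject to the flowchart that is not shown. Influence on the answers is plausible but unmeasured, and its size is unknown from the documents.

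In this trial the effect is confined to by-arm baseline summaries, the description of change in physical activity, the utility baselines, and missing baselines among anyone lost before T0. The greater reason to act is that this study exists to inform the main trial. There the CDI-2 would be the primary outcome, and its T0 value would also be post-randomisation if the schedule were copied.

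**What to change.** Once a group is formed and consented, hold the T0 session in that group and complete all T0 measures. Then trigger the web randomisation and release the arm. Amend Table 3 so that T0 precedes randomisation, and state the order in Baseline and follow-up and in Implementation. The attrition outcome already counts its 26 weeks from randomisation, so that definition need not change.

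If this order cannot be arranged, the minimum is to withhold the arm from participants and from whoever facilitates the T0 session, including the MHSW who helps with the CSRI, until T0 is complete, and to say so. If T0 is in practice already completed before allocation, correcting Table 3 is enough.

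Instruments, staff and group session stay the same, and no sample-size figure changes. The cost is a short delay between T0 and the first session, since staff set up the arm only after the allocation email. Any accelerometer wear period at T0, whose length the article does not give, would also have to finish before allocation. The delay should be kept brief, because the grouping was chosen to limit waiting and dropout.

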**Methods:**

The design is a three-arm cluster randomised controlled feasibility trial with embedded process evaluation. Participants will be help-seeking young people, aged 13–17 years experiencing mild to moderate low mood or depression, referred from three counties in England. The intervention will be delivered by registered exercise professionals, supported by mental health support workers, twice a week for 12 weeks. The three arms will be high-intensity exercise, low-intensity exercise, and a social activity control. All arms will receive a ‘healthy living’ behaviour change session prior to each exercise session and the two exercise groups are energy matched. The outcomes are referral, recruitment, and retention rates; attendance at exercise sessions; adherence to and ability to reach intensity during exercise sessions; proportions of missing data; adverse events, all measured at baseline, 3, and 6 months; resource use; and reach and representativeness.

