##### High-intensity exercise arm

This is composed of high-intensity exercises of alternating training sessions [45, 46] (e.g. basketball, football, boxing drills—see Table 1 for full breakdown) beginning with a 10-min warm up, culminating with a 5-min whole body cool down. Young people will perform four repetitions of 45 s of maximal effort exercise (> 90% predicted maximal heart rate) with 90 s rest in between each repetition (approximately 9 min). This will increase by 2 min and 15 s every 2 weeks (e.g. one repetition of 45 s of exercise and 90 s rest) for the first 6 weeks and 4 min 30 s (e.g. two repetitions of 45 s of exercise and 90 s rest) in the last 6 weeks. The final 2 weeks will be 12 repetitions (27 min of exercise). Heart rate monitors will be used to tailor each person’s maximum intensity and measure exertion in each session [47].

**Table 1 Tab1:** Exercise session outline

Week	Session number	High-intensity exercise component	Low-intensity exercise component
1	1	10 min warm up Boxing (4 reps of 45 s and 90 s rest) 5 min cool down **Total time: 24 min**	10 min warm up Walking football (7.5 min halves) *2 min rest at half time* 5 min cool down **Total time: 32 min**
	2	10 min warm up Circuit training to music (4 reps of 45 s and 90 s rest) 5 min cool down **Total time: 24 min**	10 min warm up Walking netball (7.5 min halves) *2 min rest at half time* 5 min cool down **Total time: 32 min**
2	3	10 min warm up Football (4 reps of 45 s and 90 s rest) 5 min cool down **Total time: 24 min**	10 min warm up Walking basketball (7.5 min halves) *2 min rest at half time* 5 min cool down **Total time: 32 min**
	4	10 min warm up Basketball (4 reps of 45 s and 90 s rest) 5 min cool down **Total time: 24 min**	10 min warm up Walking dodgeball (7.5 min halves) *2 min rest at half time* 5 min cool down **Total time: 32 min**
3	5	10 min warm up Choice/combination (5 reps of 45 s and 90 s rest) 5 min cool down **Total time: 26 min 15 s**	10 min warm up Walking choice (9 min halves) *2 min rest at half time* 5 min cool down **Total time: 35 min**
	6	10 min warm up Boxing (5 reps of 45 s and 90 s rest) 5 min cool down **Total time: 26 min 15 s**	10 min warm up Walking choice (9 min halves) *2 min rest at half time* 5 min cool down **Total time: 35 min**

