##### Low-intensity exercise arm

This is composed of low-intensity exercise of alternating training sessions [48] (e.g. walking football, walking netball). These activities elicit a heart rate between 40 and 50% maximal effort based on the activity compendium [49]. The sessions will follow the same warm up and cool down as the high intensity, but the overall exercise session will be longer (to energy match to high intensity). The first 2 weeks will start at 15 min of exercise with a 2-min break in the middle. This will increase by 3 min every 2 weeks for the first 6 weeks, and 6 min every 2 weeks for the second 6 weeks. The last 2 weeks will therefore consist of 38 min of exercise (including the break).

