##### Physical activity

Peak and average heart rate (Polar, H10, Polar Electro, Kempele, Finland) and rating of perceived exertion during the intervention sessions [70]. Physical activity beyond the intervention sessions by accelerometer (GENEActiv Original, Activinsights, Cambridgeshire, UK) and the Youth Physical Activity Questionnaire (Y-PAQ [71];).

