#### Statistical methods

Data analysis for the feasibility study will be largely descriptive. The referral, recruitment (> 10% of potential young people recruited), and retention (> 66% attendance at intervention sessions) will be evaluated, reporting the proportions (and confidence intervals) of young people reaching each stage of the study, by referral source and study arm. Reach and representativeness will be described in relation to the proportions of young people who are screened for participation and are randomised, and in comparison, to the characteristics of local populations. Adherence will be assessed through the proportions of sessions attended and the average heart rate achieved compared to the target for the intervention. Behaviour change, in terms of increased physical activity beyond the intervention sessions, will be measured by accelerometer and self-report data at 14 and 26 weeks. Feasibility of collecting outcome and resource use data will be evaluated by estimating the proportions of missing data in each of the outcomes assessed. The outcome measures will be summarised, by study arm, using descriptive statistics based on the intention-to-treat principle. No formal comparison of the groups will be made. To monitor safety, the number of adverse events will be reported by study arm. 

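### Average heart rate cannot show whether the high-intensity arm reached a target that applies only to its 45 s bouts

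*Protocol article*

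**What the plan says.** The Abstract lists among the trial's outcomes "adherence to and ability to reach intensity during exercise sessions", and the Feasibility outcomes section includes heart rate at each exercise session.

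The two exercise arms have different kinds of target:
- High-intensity exercise arm: "Young people will perform four repetitions of 45 s of maximal effort exercise (> 90% predicted maximal heart rate) with 90 s rest". The threshold belongs to the work bouts.
- Low-intensity exercise arm: "These activities elicit a heart rate between 40 and 50% maximal effort based on the activity compendium". The activity is nearly continuous, with a 2-minute break in the first two weeks' 15 minutes of exercise.

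The Physical activity part of the outcome measures names the summaries: "Peak and average heart rate (Polar, H10, Polar Electro, Kempele, Finland) and rating of perceived exertion during the intervention sessions". The Study schedule (Table 3) has a single matching row, "Peak and average HR". The Statistical methods section judges adherence by sessions attended and by "the average heart rate achieved compared to the target for the intervention". The Process evaluation analysis section again gives average heart rate, with session attendance, as the quantitative adherence data.

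Under Baseline and follow-up, the chest-band signal reaches the exercise professional's tablet by Bluetooth. The article then says: "It will then be entered manually into the study database by the REP". The Blinding section states that delivery staff know the allocation.

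**The concern.** The planned comparison sets a quantity that mixes work and rest against a threshold defined for work alone. In an interval protocol the two can differ widely when delivery is perfect, so a shortfall in the average says little about whether the bouts were hard enough. The other named summary, the peak, errs the other way: one bout at target gives the same peak as all of them.

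In this trial that matters. Whether young people can reach the intended intensity is a stated feasibility outcome. The Energy matching section rests the contrast between the exercise arms on intensity. Heart rate is the only instrumented measure of intensity inside the sessions, because the accelerometer is for activity outside them and perceived exertion is self-rated. A report that the high arm fell short on average could lead the team to change an intervention that was delivered as planned. It could equally hide one that was not.

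**Working it through.** **Inputs from the article.** Each repetition is 45 s of work and 90 s of rest, 135 s in all. The number of repetitions is 4, 5, 6, 8, 10 and 12 across the six two-week stages. Warm up is 10 min and cool down 5 min (High-intensity exercise arm and Table 1).

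**Reproducing the article's own timings.** 4 × 135 s = 9 min and 12 × 135 s = 27 min, as stated. Adding 15 min gives 24 and 42 min, matching Table 1. The four intermediate high-intensity totals (26.25, 28.5, 33 and 37.5 min) also match.

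**Share of time to which the target applies.**
- Interval block: 45/135 = 1/3.
- Whole session, weeks 1–2: (4 × 0.75 min)/24 = 12.5%.
- Whole session, weeks 11–12: (12 × 0.75 min)/42 = 21.4%.

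**Block average under full compliance.** The formula is (45 × work + 90 × rest)/135. The article gives no rest heart rate, so rest values are assumed.
- Work 92%, rest 60%: (41.4 + 54)/135 = 70.7%.
- Work 92%, rest 80%: (41.4 + 72)/135 = 84.0%.
- Work 90% (the threshold), rest 60–85%: 70.0–86.7%.

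**Whole-session average.** Take work at 92%, rest at 60–80%, and warm up and cool down at an assumed 55–65%.
- Weeks 1–2: (70.7 × 9 + 55 × 15)/24 = 60.9% to (84.0 × 9 + 65 × 15)/24 = 72.1%.
- Weeks 11–12: (70.7 × 27 + 55 × 15)/42 = 65.1% to (84.0 × 27 + 65 × 15)/42 = 77.2%.

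**Rest level at which the block average would reach 90%.** Rest = (3 × 90 − work)/2. This is 90%, 87.5% or 85% of maximum for work at 90%, 95% or 100%. Rest would have to be almost as hard as the bouts.

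**The average does not separate compliance from non-compliance.** Bouts at 92% with rest at 60% give (92 + 120)/3 = 70.7%. Bouts at 80% with rest at 66% give (80 + 132)/3 = 70.7%. The first participant meets the target in every bout and the second in none. All four values are assumed for illustration.

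**What the peak shows.** A participant is scheduled for 4 × (4 + 5 + 6 + 8 + 10 + 12) = 180 high-intensity repetitions over 24 sessions. Peak gives one value per session, so it can show that the target was touched in a session but not in how many of the 4 to 12 repetitions.

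**Volume of manual entry.** Two exercise arms × 3 groups × 24 sessions = 144 group sessions. With 6–9 attending, that is 864–1,296 participant-sessions, or 1,728–2,592 typed values at two each. About half belong to the low arm, where the repetition argument does not apply.

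**The case against.** The article does not define the averaging period. If the average were taken over work bouts only, the dilution would vanish, and such a definition could sit in an analysis plan not shown here. That is fair, but the Physical activity section ties both summaries to the intervention sessions. Nothing in the article limits them to bouts, so the natural reading is an average over the session or block.

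The analysis is largely descriptive, and average heart rate is considered alongside logs, observation of 5–10% of sessions and focus groups. That softens the consequence but does not make the average informative about the bout target.

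Four stronger readings are tempting, and the documents do not support them:
- A reader might infer that heart rate is retained only as two numbers and cannot be checked against source. The article is silent on whether recordings are kept, and may leave this to the full protocol or data management procedures.
- A reader might infer that entry errors would go undetected. The article describes an audit trail, data queries, central monitoring and at least one site visit. None is described as comparing entries with the device, but that falls short of showing that errors cannot be found. Unblinded entry of a device reading is a risk, not evidence of invalid data.
- A reader might infer that a promised per-repetition outcome is lost. The stated outcome is at session level, and peak partly answers it.
- A reader might infer that sessions will be formally classed as non-adherent. No heart-rate cut-off is given. The traffic-light thresholds named are attendance and questionnaire completion, although the list is not presented as complete.

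**Conclusion.** The point stands as a mismatch between metric and target in the high-intensity arm. Comparing average heart rate with a threshold above 90% would understate attainment. Under full compliance at 92%, the block average is about 71–84%, and the session average about 61–77% across the programme.

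These figures rest on assumed rest values of 60–80%, on assumed warm-up and cool-down values of 55–65%, and on an average that includes rest. The direction is less sensitive: the block average reaches 90% only if rest itself averages at least 85%, and then only with bouts at 100%. The low arm is little affected within its exercise block, since the first stage has 2 minutes of rest in 17.

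Manual entry by the deliverer is a secondary data-quality point of unknown size, because the article gives no error rate.

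**What to change.** In Statistical methods and in the Process evaluation analysis:
- For the high arm, replace the average-against-target comparison with the proportion of repetitions, or of work-bout time, in which the arm's stated target was reached.
- For the low arm, report the proportion of exercise time within its stated band.
- Derive both from the session recording already relayed to the tablet, uploaded to the study database where the application can export it.

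If export is not possible, compare the collected peak, not the session average, with the high-arm target. Report it as reached at least once in the session, and give the average as a description only, with its averaging period stated.

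Under Baseline and follow-up, make electronic export the main route into the database and keep manual entry as a backup. If the application holds only summaries, export those.

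The cost is a file upload and a short derivation in place of typing, for up to 144 group sessions. The drawbacks are handling and storing session files, marking bout start and end times, and dependence on an export function the article does not describe. The fallback needs no new data. The change concerns measurement only and takes no view on the exercise intensities.
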